#### Secondary endpoints

*Time within Target Range:* CGM data (from 50-60% of participants) will be used to assess the change in time spent within the target bG range of 72–180 mg/dl from baseline to study end. CGM data will be collected at Visits 2 (week minus 1), 7 (week 12), and 9 (week 24).

*Other Glycaemic Measures:* Glucose data from 3-day glycaemic profiles, derived from uploaded SMBG and CGM data (when applicable) will be used to assess: 1) frequency of hypoglycaemia (within 50–72 mg/dl) and severe hypoglycaemia (<50 mg/dl with associated symptoms), overall, and by defined time blocks (12:00 a.m. to 5:00 a.m., 5:00 a.m. to 10:30 a.m., 10:30 a.m. to 4:30 p.m., 4:30 p.m. to 12:00 a.m.); 2) total number of SMBG tests and average number of SMBG tests per day and by the defined time blocks; 3) percentage of all values, preprandial values (60–0 minutes prior to meal) and postprandial values (60–180minutes after start of meal) within defined bG ranges (<50 mg/dl, 50–72 mg/dl, 72–180 mg/dl, 180–300 mg/dl, #62;300 mg/dl); 4) mean bG across the 3-day profiles and for each of the 7 time points; 5) standard deviation (SD) and coefficient of variation across the 3-day profiles; 6) Mean and SD differences between preprandial and postprandial bG values over each meal in the 3-day profiles; 7) mean amplitude of glycaemic excursions (MAGE), low bG index (LBGI), high bG index (HBGI), bG risk index (BGRI) and risk for hypoglycaemia and hyperglycaemia across the 3-day profiles. The 3-day glycaemic profile data will be collected at Visits 2 (week minus 2), 5 (week 4), 7 (week 12) and 9 (week 24).

*Automated Bolus Advisor Use and Participants’ Adjustments (EXP Group):* The frequency of participants’ bolus advisor use and subsequent adjustments based on proposed bolus amounts will be derived from data uploads of the automated bolus advisor device. Analyses will include: average number of times per day participants sought advice for mealtime and correction bolus calculation; average number of times per day participants accepted the automated bolus advisor advice; average number of insulin doses adjusted up or down per day; average number of times participants accepted the automated bolus advisor responses and adjusted boluses within specific time periods (a.m., p.m., after 10 p.m.); and differences between the average number of adjusted mealtime boluses and adjusted correction boluses.

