*Participant Adherence/Use of Rule Sets:* Changes in participants’ therapy adherence to and use of rule sets in EXP participants will be derived from downloaded data obtained from automated bolus advisor devices. Adherence in CNL participants will be derived from documented therapy parameters and participants’ diaries, which are included in 3-day glycaemic profile forms. These assessments will be used to determine if participants’ adherence/use of rule sets correlates with improvement in glycaemic control. Analyses will include: average number of correctly and incorrectly used insulin-to-carbohydrate (I:CHO) rules per day for CHO intake; average number of correctly and incorrectly used insulin sensitivity factor (ISF) rules per day for bG adjustment; and number of changed I:CHO and ISF parameters compared to therapy parameters at study start (Visit 3). Data will be collected at Visits 2 (week minus 2), 5 (week 4), 7 (week 12) and 9 (week 24).

*CHO Counting:* Changes from baseline in participants’ ability to accurately count CHO will be assessed using the DAFNE plate assessment scores from Visit 1 (week minus 2) and 9 (week 24). This assessment will be used to determine if participants’ CHO counting skills correlates with improvement in glycaemic control.

*Psychosocial Outcomes*: Psychosocial outcomes including treatment satisfaction, social functioning and factors important to quality of life will be assessed using the participant questionnaire, which incorporates questions from validated psychometric instruments, as well as commonly used survey questions, to assess depression, diabetes-specific distress, diabetes self-efficacy, treatment satisfaction, health outcomes and fear of hypoglycaemia. Participant questionnaire items include: Patient Health Questionnaire depression scale (PHQ-8) [25]; Problem Area in Diabetes (PAID) [26]; Hypoglycaemia Fear Scale (HFS –II) [11];Diabetes Treatment Satisfaction Questionnaire (DTSQs, [baseline] and DTSQc [change]) [27];Gold Scale [28];and EuroQol-5 Dimensions-5 Levels measure (EQ-5D-5L) [29] (Table 2). The questionnaires will be administered at Visits 1 (week minus 2), 7 (week 12) and 9 (week 24); however, the DTSQs and DTSQc portions will be administered only at Visits 1 and 9.

**Table 2 T2:** Participant Questionnaire components

**Instrument**	**Description**	**Scoring**

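### The mealtime-versus-correction comparison and the adherence measures are defined as counts, so they mix how a participant responds to a bolus with how many boluses are taken; proportions should be added

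*Protocol article*

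**What the plan says.** The protocol article, Measures, Secondary endpoints, lists the device-derived measures for the EXP group. They include how often per day participants "sought advice for mealtime and correction bolus calculation", the "average number of times per day participants accepted the automated bolus advisor advice", the "average number of insulin doses adjusted up or down per day", and "differences between the average number of adjusted mealtime boluses and adjusted correction boluses". All are numbers; none is expressed relative to the number of boluses advised.

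The paragraph on adherence and rule sets, in the same section, defines the "average number of correctly and incorrectly used insulin-to-carbohydrate (I:CHO) rules per day for CHO intake" and the "average number of correctly and incorrectly used insulin sensitivity factor (ISF) rules per day for bG adjustment". It says these will be used to see whether "adherence/use of rule sets correlates with improvement in glycaemic control". The Primary outcome analysis section also plans Pearson correlations of the HbA1c parameters with bolus advisor parameters in the EXP group.

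Elsewhere under Secondary endpoints, glucose readings are summarised as percentages within ranges. No percentage is given for the advisor or rule-use measures.

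**The concern.** A daily count of accepted, overridden or correctly dosed boluses is the product of two things: how many boluses there were, and how the participant handled each one. The eligibility criteria set a minimum of two mealtime injections per day and no maximum, so the first factor can differ between participants. It can also differ between mealtime and correction boluses in the same participant.

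Two uses of the counts are affected. The mealtime-versus-correction contrast can be non-zero when both types of advice are treated alike, and near zero when they are treated differently. A correlation between a count and HbA1c change can reflect dosing more often rather than dosing by the rule. At stake is the interpretation of outcome 6 (adjustments to proposed boluses) and outcome 8 (adherence and use of rule sets).

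**Working it through.** The article states no figure for these measures, so there is none to reproduce. The check is algebra on the printed definitions, illustrated with assumed inputs.

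**Inputs.** M = mealtime boluses advised per day, C = correction boluses advised per day, p = probability that an advised bolus is adjusted. None is in the document. Assumed ranges: M from 2 to 4, C from 0.5 to 3, p from 0.1 to 0.3. The printed contrast does not repeat the words per day; any common time unit only rescales the result.

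**Planned contrast.** Expected adjusted boluses per day are p_meal × M and p_corr × C, so the contrast is p_meal × M − p_corr × C. With p_meal = p_corr = p this becomes p(M − C), which for p above zero vanishes only when M = C.

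| M | C | p = 0.1 | p = 0.2 | p = 0.3 |
|---|---|---|---|---|
| 3 | 1 | 0.2 | 0.4 | 0.6 |
| 4 | 0.5 | 0.35 | 0.70 | 1.05 |
| 2 | 2 | 0 | 0 | 0 |
| 2 | 3 | −0.1 | −0.2 | −0.3 |

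The reverse also occurs. With M = 3, C = 1, p_meal = 0.1 and p_corr = 0.3, the contrast is 0.1 × 3 − 0.3 × 1 = 0, although correction advice is overridden three times as readily.

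**Same contrast on proportions.** Adjusted/advised has expectation p_meal for mealtime and p_corr for correction boluses. The difference is zero whenever the two are equal, for every M and C.

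**Correlations.** If each participant accepts a share a of N advised boluses, the accepted count is about aN and the override count about (1 − a)N, so both rise with N even when a is the same for everyone. As an illustration, a simulation assumed 90 participants, 28 days, a mean of 4.5 boluses per day (between-person SD 1.2) and a constant 80% acceptance probability. The accepted count correlated about 0.99 with number of boluses, the override count about 0.84, and the acceptance proportion about 0.00. These values depend on the assumptions; the direction follows from the algebra.

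**Rule adherence.** Take two hypothetical participants: one with 3 correct and 0 incorrect uses per day, the other with 5 correct and 3 incorrect. The proportions are 3/3 = 100% and 5/8 = 62.5%. The correct count alone ranks the second higher; the two counts read together do not. The planned pair therefore holds the needed information, but a correlation run on either count separately does not use it.

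**The case against.** Several points on the other side are sound.

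- **The information is collected.** Advice sought is counted beside advice accepted and doses adjusted, and incorrect rule uses are counted beside correct ones. What is missing is a stated division. That stands, and it is why the change is cheap. It does not alter the contrast, which is expressly a difference of numbers.
- **Outcomes 5 and 6 are named as frequencies.** A count per day is a fair measure of a frequency, and the article does not claim that outcome 6 measures trust in the advice. That stands: the counts should be kept.
- **Proportions have a blind spot.** A participant who rarely consults the device but accepts every time scores 100%. That stands, and it rules out putting proportions alone into the HbA1c correlations.
- **The article is condensed and its list of analyses is not exhaustive.** An unseen analysis plan may add percentages. The point is limited to the definitions printed here.

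Two stronger readings are tempting but not supported. A reader might infer that the plan would report a difference in override behaviour that does not exist. The contrast is labelled as a difference in number of adjusted boluses, which would be real as labelled. The measure exists only in the EXP group, and the tests under Secondary outcome analyses are for comparisons between study groups, so no test of it is specified. The risk lies in how the number is interpreted.

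A reader might also infer that boluses "within specific time periods (a.m., p.m., after 10 p.m".) are counted twice late in the evening, because p.m. contains the last period. Three separate bins are the natural reading, and nothing says that the periods overlap or are compared with one another.

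**Conclusion.** The point holds as a modest improvement to secondary measures. As printed, the mealtime-versus-correction contrast equals p(M − C) under equal override probability and so combines override behaviour with bolus volume. Correlations of the acceptance, override or correct-use counts with HbA1c inherit the same mixture; this takes the bolus advisor parameters in the Primary outcome analysis section to include those counts.

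The algebra needs no assumed values, but size and sign do. The contrast is 0.2 to 0.6 per day for M = 3, C = 1 and p of 0.1 to 0.3, negative for M = 2 and C = 3, and zero if M = C. The document does not say which case applies. The primary HbA1c comparison and the sample size are not affected.

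**What to change.** 1. Define the mealtime-versus-correction contrast as the within-participant difference in the proportion adjusted: adjusted/advice requested, calculated separately for each bolus type and pooled over the participant's days.
2. Define rule adherence as correct/(correct + incorrect) uses, for the I:CHO and ISF rules separately.
3. Include these proportions in the planned HbA1c correlations alongside the counts per day. Keep the counts as the measure of frequency for outcomes 5 and 6; they also show under-use of the device, which a proportion hides.

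**Cost.** Wording and a few derived variables, with no new data collection. The device uploads supply the EXP numerators and denominators, and the planned contrast already requires adjusted boluses to be classed by type. For CNL, the 3-day forms record meals with their carbohydrate content and the prandial and correction doses. The drawback is unstable percentages for participants with few correction boluses. Pooling over days reduces this, and the number of boluses behind each percentage should be shown.

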### Procedure

EXP participants will utilise the Accu-Chek® Aviva (Roche Diagnostics, Indianapolis, USA), which incorporates an automated bolus advisor into a blood glucose meter. Users can obtain prandial and correction bolus recommendations based upon a current blood glucose value, planned carbohydrate intake and individualised therapy parameters stored in the device. The device automatically calculates the appropriate bolus for the user and stores blood glucose and meal information in an electronic diary. A previous study [24] showed that the automated bolus advisor device can assist people in achieving desired postprandial glucose control without significant hypoglycaemia.

Physicians and staff in both arms will be informed about the clinical investigational plan, including the rationale for the study, design of the study protocol, subject-related procedures, and use of evaluation questionnaires. EXP physicians and staff will receive training on using the automated bolus advisor device to set insulin parameters and download SMBG and insulin dosing data.

Approximately 50-60% of the sites (those with prior experience of CGM use) will utilise a blinded continuous glucose monitoring (CGM) device (DexCom Seven® Plus, DexCom, Inc., San Diego, California, USA), with data uploaded directly to a designated secure server. Clinicians and participants will not have access to this CGM data for the duration of the study, which will be analysed centrally to contribute to the secondary end-points of the study.

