#### Visit 1: screening and training (week – minus 2)

At Visit 1, investigators will confirm participants’ eligibility for the study (based on inclusion/exclusion criteria), obtain written informed consent, record demographic information, collect relevant medical history/lifestyle information, document all current medications, perform physical examinations, measure and record weight, height, blood pressure, heart rate, collect blood and urine samples for laboratory tests (HbA1c, urinalysis, chemistry panel with lipids, full blood count [FBC]) and perform pregnancy testing (for women of child bearing age). Participants will be asked to complete a questionnaire that incorporates the questions from standard psychometric instruments (See *Measures* section).

Investigators will use standardised worksheets to assess participants’ knowledge and skills relevant to MDI therapy and CHO counting. Selected Dose Adjustment For Normal Eating (DAFNE) plates will also be used in the CHO counting assessment. Deficits in MDI therapy and CHO counting skills will be documented and addressed during Visit 2.

Participants in both groups will initially receive a blood glucose meter (Accu-Chek® Nano blood glucose meter, Roche Diagnostics, Indianapolis, Indiana, USA) and will be thoroughly trained in its operation. Where applicable, investigators will connect the CGM device to subjects and provide training.

Participants will be instructed to generate 7-point glycaemic profiles (preprandial/2-hours postprandial at all meals, and bedtime) over 3 consecutive days and document their results on a standardised form that will be provided. Using the form, participants will also document details of their meals (including number of CHOs), physical exercise (intensity and duration), basal insulin doses, prandial bolus doses, and correction bolus doses over the 3-day testing period. CGM participants will be instructed to wear their device until Visit 2. This will be done in addition to completing their 3-day, 7-point glycaemic profiles.

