#### Visit 3: training and therapy initiation (week – 0)

At Visit 3, investigators will collect participants’ bG meters, upload bG meter data to the secure server; download meter data to clinic software, and prepare printouts of bG data to review with participants. New AE/SAEs or changes to ongoing AE/SAEs since the last visit will be assessed and concomitant medications updated. Investigators will use the therapy parameter cards and instruct participants on how to use their parameters.

EXP participants will be given their automated bolus advisor device (Accu-Chek® Aviva Expert bG meter, Roche Diagnostics, Indianapolis, Indiana, USA) and instructed to discontinue use of their current bG meter. Investigators will conduct 1-hour training sessions in automated bolus advisor device use and update the devices with each participant’s new therapy parameters.

At the conclusion of the visit, all participants will receive SMBG supplies and a logbook with a 3-day glycaemic profile form. Participants will be instructed to complete the 3-day profiles one week prior to Visit 5.

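### Rule-set adherence is recorded from the device in EXP and from 3-day-form diaries in CNL, so the between-arm comparison confounds behaviour with recording method, in a direction and by an amount the protocol does not settle

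*Protocol article*

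**What the plan says.** Change in therapy adherence and use of rule sets is the eighth listed secondary outcome (protocol article, Methods/design). The Secondary endpoints section, under Participant Adherence/Use of Rule Sets, fixes the data source by arm:

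- EXP: "use of rule sets in EXP participants will be derived from downloaded data obtained from automated bolus advisor devices".
- CNL: "Adherence in CNL participants will be derived from documented therapy parameters", together with participants' "diaries, which are included in 3-day glycaemic profile forms".

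The same measures are then defined for both arms. The first is the "average number of correctly and incorrectly used insulin-to-carbohydrate (I:CHO) rules per day for CHO intake". The second is the corresponding count for insulin sensitivity factor (ISF) rules. The third is the number of I:CHO and ISF parameters changed since Visit 3. Data are collected at Visits 2, 5, 7 and 9, and the results are to show whether adherence correlates with better glycaemic control.

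Four other places bear on this:

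- Design: both arms are to be assessed with the same instruments at the same times.
- Procedure: the EXP device calculates the bolus and "stores blood glucose and meal information in an electronic diary".
- Visit 3: EXP participants first receive the device here, and "all participants will receive SMBG supplies and a logbook with a 3-day glycaemic profile form".
- Secondary outcome analyses: the remaining secondary outcomes are compared by group at each visit and for changes between visits, with two-sample t-tests or chi-square tests. Pearson correlations are planned among all variables of interest.

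**The concern.** Recording method is completely aliased with treatment arm. No covariate adjustment can separate what participants did from how it was recorded, because no participant in either arm is measured the other way after Visit 3. The article describes no common-source analysis and no check of one source against the other.

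Baseline does not rescue the comparison. The EXP source named in the article does not exist at Visit 2. EXP change in the two rule-use counts must therefore either lack a baseline or run from a form to a device log, while CNL stays on the form throughout.

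At stake is the interpretation of one listed secondary outcome. A difference in rule use could reflect behaviour, recording, or both, and the data collected as described could not tell which. This is not detail left to a fuller document: the article itself assigns the source by arm.

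**Working it through.** **1. No figure to reproduce.** The article gives no expected value, SD or difference for adherence. The check is first structural, then illustrative.

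**2. What the contrast estimates.** Let T be true rule use, f the average recording error of the form and g that of the device log.

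- Level at Visits 5, 7 or 9: EXP records T_E + g and CNL records T_C + f. The difference is (T_E − T_C) + (g − f).
- Change from Visit 2, taking the form as the EXP baseline: EXP change is ΔT_E + (g − f) and CNL change is ΔT_C + (f − f). The difference is (ΔT_E − ΔT_C) + (g − f).

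Subtracting baseline leaves the term g − f in place, since it enters at follow-up in EXP only.

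**3. Sign of g − f.** The outcomes are counts per day. A dose or carbohydrate value missing from a diary may lower the correct count, the incorrect count or both, and the article gives no scoring rule for missing entries. Equally, doses decided without the advisor may be absent from the EXP log; frequency of advisor use is itself an outcome, so full use is not assumed. The sign is therefore open.

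**4. Which measures are exposed.** The two rule-use counts are. The changed-parameter count is referenced to Visit 3, when EXP has the device, so it is much less exposed.

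**5. Illustration of size.** Inputs: 90 per arm (Primary outcome analysis); two-sided 5% t-test (assumed, as the article does not state sidedness for secondary outcomes); no true difference; recording offset b = (g − f)/SD, assumed.

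Noncentrality = b × √(n/2) = b × √45 = 6.708b. With 178 degrees of freedom, the rejection probabilities are:

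| Assumed b | Noncentrality | Rejection probability |
|---|---|---|
| 0 | 0 | 5% |
| 0.2 | 1.34 | 27% |
| 0.4 | 2.68 | 76% |
| 0.6 | 4.02 | 98% |

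These are powers against a chosen bias. They show how sensitive the test is to an offset, not that such an offset exists.

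**6. Correlation with HbA1c change.** Suppose the arms are pooled, adherence and HbA1c change are unrelated within arm, and the treatment effect is the planning value d = 0.5/0.9 = 0.556 SD. The induced correlation is

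r = (b·d/4) / √[(1 + b²/4)(1 + d²/4)].

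| Assumed b | Induced r | Rejection rate (4,000 simulated trials) |
|---|---|---|
| 0.2 | 0.03 | 6% |
| 0.5 | 0.07 | 14% |
| 0.8 | 0.10 | 26% |

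Within EXP alone, a constant offset leaves the rejection rate near 5%.

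**The case against.** The strongest reply has five parts.

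- **Direction.** A reader might infer that the plan must favour EXP, because diary gaps would count as errors. The documents do not support that, since no such scoring rule is stated and under-recording is possible in both arms. This part of the reply stands.
- **Device effect.** A reader might also infer that accepted advice is correct by construction and so is pure artefact. It is not. If the device applies the participant's parameters and the advice is followed, the rule really was used correctly, which is the intended mechanism. A common recording method would still show it. Only the difference in recording is an artefact.
- **Magnitude.** The percentages rest on assumed offsets and are not evidence about this trial. That is right, and they are offered only as an illustration.
- **Correlation.** The article does not say that arms are pooled. It does restrict only the bolus advisor parameters to EXP, which suggests pooling elsewhere, but this is not explicit. Even if pooled, the distortion is modest.
- **Importance.** This is one of nine listed secondary outcomes, in a group compared descriptively, with no power claim attached. That limits the weight of the point.

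What remains untouched is the mismatch itself. The sources differ by arm, the EXP source is unavailable at Visit 2, and a between-group test is planned on the result.

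**Conclusion.** The point holds for the counts of correctly and incorrectly used I:CHO and ISF rules. As described, their between-arm comparison confounds behaviour with recording method, conflicts with the Design section, and is not repaired by using change from baseline. The bias may run in either direction and its size cannot be derived from the article. Offsets as small as 0.2 SD, if present, would raise the false-positive rate from 5% to about 27% with 90 per arm.

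The changed-parameter count is much less exposed. A pooled correlation with HbA1c would be affected only modestly. The primary endpoint, HbA1c from a central laboratory, is unaffected. The plan should be changed, but the point does not threaten the trial's main conclusion.

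**What to change.** Base the between-arm comparison of rule use on the 3-day profile forms in both arms at Visits 2, 5, 7 and 9, scored with one algorithm that also states how missing entries are handled. Make sure that EXP participants complete the carbohydrate and dose fields after Visit 3. The article spells these fields out only for the screening profile at Visit 1. Report device-log adherence as a description of EXP alone, and compute correlations between adherence and HbA1c within arm.

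The forms are already issued to all participants, so the cost is scoring the EXP forms and revising the analysis wording. There are two drawbacks. EXP would contribute only three days per visit to the comparison rather than all device days. EXP participants may also copy entries from the device, so a common form reduces the recording difference but may not remove it.

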*Patient Health Questionnaire 8 (PHQ-8)*[25]	Self-report measure of depression	Each of 8 items scores from 0=‘not at all’ to 3=‘nearly every day’ Major depressive disorder (PHQ-8): ≤ 4 – no significant symptoms, 5 to 9 – mild symptoms, 10 to 14 – moderate symptoms, 15 to 19 – moderately severe symptoms, ≥ 20 – severe symptoms
*Problem Area in Diabetes (PAID)*[26]	Covers a range of emotional states frequently reported in diabetes. It is primarily a measure of diabetes-specific emotional distress	Each of 20 items scores from 0=‘not a problem’ to 4=‘serious problem’ PAID summary score: 0 to 39 – no distress, 40 to 59 – mild distress 60 to 79 – moderate distress 80 to 100 – severe distress
*HFS II (Hypoglycaemia Fear Scale)*[11]	Provides an assessment of an individuals’ fear of hypoglycaemia both overall and in terms of behaviour and worry. IUsed to assess both fear of hypos and maladaptive behaviours to avoid them.	Each of 33 items scores from 0=‘never’ to 4=‘always’ Score for frequency/severity of avoidance behaviour: 0 to 36 – no/slight avoidance behaviour: 37 to 48 – moderate avoidance behaviour: 49 to 60 – frequent/severe avoidance behaviour Score for severity of worry: 0 to 43 – no/slight worry: 44 to 57 – moderate worry: 57 to 72 – frequent/severe worry
*Diabetes Treatment Satisfaction Questionnaire (baseline) DTSQs and DTSQc (change)*[27]	Baseline version measures patient satisfaction with diabetes treatment Change version developed to overcome ceiling effects with treatment satisfaction	DTSQs -- Each of 6 items scores from 0=‘very bad’ to 6=‘very good’ DTSQc -- Each of 6 items scores from −3=‘much worse now’ to 3=‘much better now’)
*Gold Scale*[28]	Categorises awareness of having reduced awareness of hypoglycaemia in patients with diabetes.	One item with score from 1=‘always aware’ to 7=‘never aware’ Impaired awareness if the Gold scale score is ≥4
EuroQol-5 Dimensions-5 Levels measure *(EQ-5D-5L)*[29]	Measures health outcomes and is applicable to a wide range of health conditions and treatments	Each of the 5 items score from 1=‘no problems’ to 5=‘unable’) EQ-5D health assessment scores from 0=‘worst health’ to 100=‘best health’)

All scales and measures used in the study will contain participant codes rather than participant identifiers. Participant identifiers will be restricted to their clinicians and senior investigators.

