#### Secondary outcome analyses

Statistical analysis of change in time spent within target range will be performed according to the same schemata used for the primary outcome. Other secondary outcome variables will be compared descriptively by study groups for each scheduled visit and for changes between visits. Continuous variables, including scores from the questionnaires will be summarised using N, mean, SD, median, lower and upper quartile, minimum and maximum; categorical variables will be summarised using counts and percentages of participants in each category. Two-sample t-tests in the case of continuous variables and chi-square tests in the case of categorical variables will be performed for group comparisons. Graphical techniques will be used to display changes over time, if appropriate. Pearson correlation coefficients will be computed between all variables of interest.

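### The plan does not say which DTSQ version is given at which visit, and its change analyses make no exception for DTSQc, which is already a change score

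*Protocol article*

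**What the plan says.** **Schedule.** In the protocol article, Secondary endpoints (Psychosocial Outcomes), the questionnaires are given at Visits 1, 7 and 9, with this restriction: "however, the DTSQs and DTSQc portions will be administered only at Visits 1 and 9". The same paragraph labels the two versions "DTSQs, [baseline] and DTSQc [change". The visit descriptions do not separate them. Visit 1 refers to a single combined questionnaire, and the text for Visits 5 through 9 mentions only patient questionnaires at Visits 7 and 9.

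**Scales.** Table 2 gives "DTSQs -- Each of 6 items scores from 0=‘very bad’ to 6=‘very good" and "DTSQc -- Each of 6 items scores from −3=‘much worse now’ to 3=‘much better now". It explains the second form as follows: "Change version developed to overcome ceiling effects with treatment satisfaction".

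**Analysis.** Secondary outcome analyses states: "Other secondary outcome variables will be compared descriptively by study groups for each scheduled visit and for changes between visits". Time in target range has its own rule. Questionnaire scores fall under the general one: "Continuous variables, including scores from the questionnaires will be summarised", with two-sample t-tests between groups. Primary outcome analysis adds two further uses of the psychosocial summary scores. They are possible baseline covariables for HbA1c change, and both the scores and their changes from baseline are to be correlated with the HbA1c parameters. Neither section mentions DTSQc separately.

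**The concern.** A status questionnaire and a change questionnaire need different handling. A status score has to be measured twice before a change can be formed. A change score is measured once, at the end, and is the change. The article sets one schedule for both forms and one set of change analyses for all questionnaire scores, so it does not keep the two apart.

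Treatment satisfaction is part of the stated hypothesis and is named within the ninth secondary outcome. A site or programmer following the text literally would collect a DTSQc score at screening, before the Visit 2 skills training and randomisation and before the bolus advisor is issued at Visit 3, and would then subtract it. One following the labels would have no like-for-like pair and might difference across versions. A form not handed out at Visit 9 cannot be recovered later.

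**Working it through.** The plan states no figure for the DTSQ, so there is nothing to reproduce. The check sets the schedule, scales and analysis rules against each other under the two possible readings.

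**Inputs.** Table 2 gives six items scored 0 to 6 (DTSQs) and six items scored −3 to 3 (DTSQc). It does not say that items are summed; I assume they are, for illustration only.
- DTSQs total: 6 × 0 = 0 to 6 × 6 = 36.
- DTSQc total: 6 × (−3) = −18 to 6 × 3 = 18.

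**Literal reading: both versions at Visits 1 and 9.**
- DTSQs, Visit 9 minus Visit 1: same scale, valid.
- DTSQc at Visit 9, between arms: valid.
- DTSQc at Visit 1: no study treatment to refer to. It would still qualify as a baseline covariable.
- DTSQc, Visit 9 minus Visit 1: a difference of change scores, one of them without a reference point.

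The last item costs precision. If the Visit 1 SD is k times the Visit 9 SD and the correlation is r, the SD of the difference relative to the Visit 9 SD is √(1 + k² − 2rk). The documents give neither k nor r, so the following are assumptions:
- k = 1, r = 0: √2 = 1.41
- k = 0.5, r = 0: √1.25 = 1.12
- k = 1, r = 0.5: √1 = 1.00

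Because Visit 1 precedes randomisation, the expected arm difference in the Visit 1 score is zero. Subtracting it therefore adds noise to the between-arm contrast, not bias.

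**Label reading: DTSQs at Visit 1, DTSQc at Visit 9.**
- DTSQc at Visit 9, between arms: valid, and already the change.
- A DTSQ change from baseline or between visits: not available, because neither version is repeated.

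The only difference that could be formed is across versions, DTSQc minus DTSQs. Three hypothetical participants show that it means nothing for an individual:
- DTSQs 30, then DTSQc 0 (no change): 0 − 30 = −30
- DTSQs 30, then DTSQc +12 (improved): 12 − 30 = −18
- DTSQs 10, then DTSQc −5 (worse): −5 − 10 = −15

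The participant who improved ranks below the one who got worse. Such misranking would matter most for the planned correlations with HbA1c. Between arms, randomisation again makes the expected contribution of the baseline term zero.

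**Side by side.** The Visit 9 comparison of DTSQc between arms is valid under both readings, and Secondary outcome analyses plans it through its provision for each scheduled visit. What fails is limited to the change-from-baseline and between-visit use of DTSQc, any use of DTSQc as a baseline covariable, and any difference across versions.

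**The case against.** The strongest reply is that the labels settle the schedule. One version is marked as baseline and the other as change, so the sentence naturally means DTSQs at Visit 1 and DTSQc at Visit 9, and its purpose is only to say that the DTSQ is skipped at Visit 7. On that view no variable is measured twice, the general rule on changes yields nothing for the DTSQ, and nobody would subtract one form from the other. In addition, this is a condensed article, the visit schedule figure is not shown, and the full protocol may assign the forms.

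Much of this stands. The labels do favour one version per visit, and no sentence orders DTSQs to be subtracted from DTSQc. The cross-version examples therefore show what to avoid, not what the plan prescribes.

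Two things remain. The sentence as written names both versions and both visits without pairing them. The change rule is also more than one loose sentence: Secondary outcome analyses applies it to the remaining secondary outcomes, and Primary outcome analysis applies changes from baseline specifically to the psychosocial summary scores. Neither exempts a score that is already a change. The point rests on what the article states, not on what it leaves out.

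**Conclusion.** The point holds as a minor correction to one secondary outcome. The schedule does not assign a DTSQ version to each visit, and the change analyses, read as written, either use a Visit 1 DTSQc that cannot be interpreted or call for a DTSQ change that cannot be formed on one scale.

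A reader might infer that treatment satisfaction therefore cannot be read at all, or that both forms are definitely given together at screening. The documents support neither. The planned Visit 9 comparison of DTSQc is sound under both readings, the change in DTSQs is also sound under the literal one, and the labels point away from joint administration.

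The size cannot be fixed from the documents. The summed ranges assume added items. The 1.41 factor assumes equal SDs and zero correlation, and with a correlation of 0.5 the penalty disappears. The primary endpoint, the sample size and the safety analyses are unaffected.

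**What to change.** 1. In Secondary endpoints, state that DTSQs is given at Visit 1 and DTSQc at Visit 9 only.
2. In Primary outcome analysis and Secondary outcome analyses, exclude DTSQc from every change-from-baseline and between-visit analysis and from the baseline covariables, and rule out differences across the two versions.
3. State that Visit 9 DTSQc is compared directly between arms, adjusted for the Visit 1 DTSQs score. This replaces an unadjusted t-test with one that uses a baseline measurement the trial already collects.
4. Repeat DTSQs at Visit 9 only if a change in DTSQs is to be reported.

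The cost is a few sentences. If the label reading was intended, data collection does not change. If the literal reading was intended, six DTSQc items drop out at Visit 1. The optional step means six DTSQs items at Visit 9, which are extra only under the label reading. Items 2 and 3 can be applied whichever forms have been collected, provided DTSQs was obtained at Visit 1 and DTSQc at Visit 9.
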